## Abstract

The treatment of early triple-negative breast cancer (eTNBC) has improved patients’ prognosis but often leads to adverse events and sequelae affecting quality of life (QoL). Pain Neuroscience Education (PNE) is a promising non-pharmacological intervention in this field. Preliminary data have shown the beneficial effect of PNE in BC survivors. However, there are still gaps in knowledge regarding its optimal use in eTNBC. To address this issue, a prospective pilot study will enroll 30 consecutive patients diagnosed with eTNBC at IRCCS Humanitas Research Hospital. The PNE program will consist of 10 weekly sessions to be started within 4 weeks of the onset or worsening of a pain syndrome (PS). QoL, pain, and disability will be assessed before, during, at the end of, and 6 months after PNE using validated questionnaires. Peripheral venous blood samples will be taken before and at the end of PNE to evaluate inflammatory serum biomarker levels. The primary objective is to evaluate whether PNE leads to clinical improvement in QoL and pain. If successful, it will be validated in a larger multi-centric cohort, potentially leading to its widespread implementation as a standard pain management tool for eTNBC patients.

## 1. Introduction

Scientific advancements in oncology have significantly improved the prognosis of early-stage breast cancer (BC) patients through the integration of locoregional (i.e., surgery and radiotherapy) and pharmacological treatments [1]. On the other hand, these treatments increase the risk of sequelae and complications, both short- and long-term, with a significant impact on patients’ quality of life (QoL) [2,3].

Premenopausal women are more likely to develop triple-negative BC (TNBC) [4], though the incidence might vary based on a number of factors, including genetic susceptibility, family history, and lifestyle [5]. Since TNBC is more frequently diagnosed in young, professionally and socially active women, they are generally more inclined to participate in educational therapies aimed at improving their well-being [6]. Regarding side effects, patients with TNBC are more likely to be exposed to more extensive breast surgery (i.e., in the case of BRCA pathogenic variants) and perioperative chemotherapy treatments (neoadjuvant and/or adjuvant) containing anthracyclines and taxanes, which are associated with a high incidence of painful syndromes (PSs) [7].

PSs are the most common comorbid conditions in oncology, greatly impacting patients’ QoL [2,3]. These syndromes, including direct tumor-related pain or pain resulting from treatments, can be multifaceted and can also worsen pre-existing conditions, such as headaches, which are common in younger female patients [8]. Therefore, managing these syndromes is a significant issue for BC patients, especially those with TNBC.

Persistent postoperative pain, a form of neuropathic pain, is a common post-treatment PS, affecting 11 to 57% of patients and often lasting more than three months after surgery [9], especially in TNBC patients, who often require mastectomies and the use of chemotherapeutic agents (such as taxanes and carboplatin) in their therapeutic algorithm, with a notable incidence of post-treatment PSs [10,11]. These agents can cause peripheral sensory neuropathy, particularly in the extremities, which may persist beyond the end of treatment. The incidence of taxane-related neuropathy varies between 30% and 97%, with a persistence rate of up to 40–50% six years after treatment [7]. This neuropathy often manifests as numbness, tingling, and weakness, impairing patients’ daily activities and QoL. Neuropathy can also lead to difficulties with balance and coordination, increasing the risk of falls and injuries [12].

The mechanisms behind PSs in BC are unclear, but research indicates that they may arise from dysregulation of the immune system and neurotransmitters. Cancer is associated with systemic inflammation, and many of its symptoms, including pain, can be attributed to the action of inflammatory cytokines released during the inflammatory process on the peripheral and central nervous systems [13]. In healthy individuals, there is a balance between pro- and anti-inflammatory cytokines, but in cancer patients, this balance is often disrupted. Recent studies have shown that pro-inflammatory cytokines play a significant role in mediating cancer pain by releasing mediators that sensitize nearby nociceptors to painful stimuli and evoke central responses. Some inflammatory markers, such as C-reactive protein (CRP) and erythrocyte sedimentation rate (ESR), are elevated in BC patients and are associated with a worse prognosis [14,15,16]. Moreover, serum levels of certain pro-inflammatory cytokines have been proportionally correlated with the severity of BC-related pain [17]. Lastly, the neutrophil-to-lymphocyte ratio (NLR) is considered a potential prognostic biomarker suitable for assessing the extent of systemic inflammation, contributing to the development of pain and BC progression [18].

Headaches, particularly migraine, are a common pre-existing PS among BC patients. A recent study of 440 patients showed that the prevalence of migraine in BC patients is much higher than expected for the same age group in the general population. Furthermore, this study showed that BC occurs earlier in patients with migraine and that locoregional treatments (especially radiotherapy) can exacerbate the number of headache days in patients with this pre-existing condition. Finally, patients with migraine and tension-type headaches have a higher risk of developing taxane-induced neuropathy. [8]. The Calcitonin Gene-Related Peptide (CGRP), a pro-inflammatory neurotransmitter, plays a significant role in the pathophysiology of migraine and has been found to be increased in migraine patients. Inhibiting CGRP has shown promise in managing migraine pain, and intriguingly, CGRP is also implicated in BC, influencing cell proliferation, differentiation, and angiogenesis [19,20]. It has a U-shaped effect on BC cells, with inhibitory actions at low concentrations and activating effects at high concentrations [21].

There is emerging research into the potential impact of non-pharmacological treatments on BC comorbid conditions. Among these non-pharmacological interventions, Pain Neuroscience Education (PNE) appears promising. PNE aims to help patients understand pain in its full context, emphasizing its emotional, cultural, psychological, and social aspects. The goal is not just to reduce pain but also to improve patients’ physical, emotional, and social functioning. PNE, recognized by the World Health Organization, includes educating patients about pain mechanisms, enhancing coping strategies, and improving the QoL of patients with persistent pain [22].

PNE is aimed at changing patients’ beliefs about pain and its origins, functions, biological processes, and perception-altering factors. The intention is to help patients move away from the purely biomedical perception that pain equals damage and understand it as a multidimensional experience influenced by a network of various central nervous system areas. PNE has been extensively studied in patients with different forms of chronic pain and shown to have positive effects on pain, disability, catastrophizing, and physical performance [23,24].

Preliminary data also suggest that PNE can be useful in patients undergoing surgery for BC. The first pain education programs studied for BC patients were mainly digital. One study showed patient satisfaction and an association between the intervention and a shorter duration of opioid use after surgery, though no significant improvement in pain-related disability, pain intensity, and physical or emotional functioning was observed [25]. Another study supported a personalized eHealth intervention that improved pain-related functioning, physical functioning, and QoL in women with persistent pain after BC treatment. However, the optimal program and mode of PNE administration for these patients are yet to be established [26]. A meta-analysis investigating the effect of patient education in BC survivors reported a short-term improvement in overall QoL, emotional health, and fatigue but a non-significant decrease in pain severity [27].

Overall, the pharmacological management of PSs remains unsatisfactory for patients with TNBC, partly due to oncologic treatments that may intensify these syndromes. In this study, we plan to examine the effectiveness of a program that combines PNE and cognitive training. Although PNE has been effective for many chronic pain conditions, its use has not been tested in cohorts of TNBC patients. We anticipate that it will enhance coping strategies, reduce disability, and improve patients’ QoL.

## 2. Materials and Methods

### 2.1. Study Design

This mono-centric, observational, prospective, pilot cohort study is being led by IRCCS Humanitas Research Hospital in Rozzano, Italy. The study was approved by the IRCCS Humanitas Research Hospital Ethics Committee (protocol identification number: ONC/OSS-17/2023, v.1.1). All patients will sign an informed consent form in accordance with the Declaration of Helsinki.

Our study protocol is presented according to the SPIRIT (Standard Protocol Items: Recommendations for Interventional Trials) checklist (File S1) [28]. 

### 2.2. Participants

This pilot study will enroll patients diagnosed with early-stage TNBC at the IRCCS Humanitas Research Hospital. They will be given a web link to complete a monthly pain questionnaire. Those with a Numeric Rating Scale (NRS) ≥4 will be invited to join the study within 4 weeks of the onset or worsening of the pain syndrome. 

Specifically, the inclusion criteria for patients in the study will be the following:Age >18 years;A willingness to participate in the proposed study;Female sex;A histologically confirmed diagnosis of TNBC;Stages I–III;Indicated for neoadjuvant or adjuvant treatment with anthracyclines and taxanes +/− immunotherapy (i.e., pembrolizumab);NRS ≥4;The ability to provide informed consent according to the International Conference on Harmonization (ICH)—Good Clinical Practices (GCP) and national/local regulations.

The exclusion criteria will be as follows:
The recent introduction of analgesic therapies for PSs, with the frequent or continuous use of pain therapies (including non-steroidal anti-inflammatory drugs, steroids, opioids) for chronic PSs; patients on any analgesic therapy will be recruited only if the therapy is stable for at least 3 months;Patients eligible for other therapeutic regimens (e.g., cyclophosphamide, methotrexate, 5-fluorouracil);Patients who have received or are receiving endocrine therapies for oncological or non-oncological reasons (as these can cause PSs and would represent a potential confounding factor);Patients with a strong language barrier;The diagnosis of a second primary synchronous or metachronous neoplasm (within 5 years prior to the diagnosis of TNBC);The diagnosis of a chronic PS secondary to orthopedic, neurological, or rheumatological disease.

Patients will be allowed to modify their pain management strategies, including analgesic medications, as needed. These adjustments will be documented, and such patients will continue to be monitored and included in the study’s analysis, with appropriate statistical adjustments made to account for any changes in their analgesic use, assessed by applying an equianalgesic scale.

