### 2.3. Participant Recruitment and Study Procedures

This project will involve the consecutive enrollment of early TNBC patients with the onset or worsening of a PS (NRS ≥4) who meet the inclusion criteria of the study. 

The evaluation of QoL, perceived pain, and disability will be carried out at baseline (T0) and approximately 5 weeks after the start (T1) and at the end (T2) of PNE; finally, an additional assessment will be performed 6 months after the end of PNE. This evaluation will be conducted using validated questionnaires that measure the overall QoL of BC patients (European Organization for Research and Treatment of Cancer Quality of Life Questionnaire, Breast Cancer-Specific 23 [EORTCQLQ-BR23] questionnaire), pain (NRS), migraine and headaches (Headache Impact Test-6 [HIT-6] and MIgraine Disability ASsessment [MIDAS] questionnaires), and anxiety and depression (Hospital Anxiety and Depression Scale [HADS]).

At timepoints T0 and T2, a peripheral venous blood draw will be collected for the execution of a panel of blood chemical tests (CRP, ESR, Interleukin [IL]-6, IL-8, tumor necrosis factor [TNF]-α, and CGRP, as well as NLR calculation).

Our program involves the administration of a 10-session PNE program on a weekly basis (total of 10 weeks of intervention), in addition to the standard of care, according to the level of pain. The PNE sessions will be conducted by a physiotherapist expert in delivering PNE across different chronic pain populations, with more than 10 years of experience. Each session will be delivered in small groups (3–5 people) using a PowerPoint slide presentation and will last approximately one hour. A part of each session will be dedicated to questions and answers and personal discussion about personal experience.

The contents of the 10 sessions will be as follows:The concept of pain and its biological function.Common misconceptions about pain and its origin.The basics of the neurobiology of pain.What factors alter the perception of pain?The concept of the nervous system as a “protomet” and other metaphors.What happens when pain persists and becomes chronic?How can I train my nervous system?The importance of context, emotional aspects, and communication.The importance of stress management.Long-term pain management.

The program was structured starting from the books “*Explain pain*” [29] and “*Explain pain supercharged*” [30,31], written by the leading researchers on the topic of PNE.

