### 2.4. Objectives

Primary objective:The primary objective of the project is to evaluate, through the use of validated questionnaires, whether the implementation of a dedicated PNE and cognitive training program can lead to clinical improvement in terms of QoL and pain in patients with early-stage TNBC.

Secondary objectives:To assess the impact of PNE on headaches/migraine in patients affected by this condition prior to the start of the program.To evaluate the impact of PNE on anxiety/depression symptoms according to the score of the planned scales.To investigate whether serum levels of inflammatory biomarkers correlate with PSs.To investigate whether serum levels of inflammatory biomarkers before and after PNE treatment correlate with the response to PNE.To compare the results at the end of PNE (T2) with those at six months after the end of the program.

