#### 2.7.2. Analysis

Detailed clinical and demographic variables will be recorded for each patient. Frequency tables and descriptive statistics (mean, standard deviation, percentage, median, range) will be used to summarize patient characteristics. 

Both the total score and the score for each domain will be calculated for each questionnaire, according to the nature of the questionnaire. The expected overall clinical improvement will be assessed based on the variation in the total scores of the administered assessment questionnaires at different timepoints (T0, T1, and T2). A positive response to PNE is defined as a 50% or greater improvement in patient-reported outcomes.

Changes in the levels of serum biomarkers between T0 and T2 (baseline and end of training) will be separately analyzed among patients who have responded to PNE (defined as an improvement in patient-reported outcomes of at least 50%) compared to non-responders using a generalized linear model in which the factors involved in the analysis will be the groups (responders/non-responders) and the timepoints (intra-group variable).

As variables of interest and covariates, demographic data, education level, comorbidities, risk factors for BC (e.g., body mass index, cigarette smoking), and menopausal status at diagnosis will be recorded. Additional covariates to be considered include anxiety and depression, which are closely linked to the perception of pain and the experience associated with it.

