## 3. Discussion

In this study, we plan to examine the activity of a program that combines PNE and cognitive training. We anticipate that it will enhance coping strategies, reduce disability, and improve patients’ QoL.

Thus, the present study will improve the knowledge on the feasibility of administering a PNE protocol to BC patients and, specifically, to early TNBC patients, providing data on the efficacy of PNE in reducing pain and improving patients’ QoL. To our knowledge, this study is the first to test a PNE intervention in early TNBC patients under treatment. To date, only a few clinical trials have investigated the potential efficacy of PNE in reducing chronic postoperative pain in BC patients, with conflicting results [40,41,42,43]. Among the completed trials, only the study by Manfuku and colleagues demonstrated a statistically significant effect of PNE in decreasing pain [43]. Possible biases in the selection criteria could explain the lack of reliability among study findings, for example, the inclusion of patients experiencing low pain intensity. To overcome this issue, we will include only BC patients who experience at least a moderate level of pain (i.e., NRS ≥4). This issue was also addressed in the PaiNEd trial, in which the research group added an inclusion criterion of a visual analog scale ≥ 4 in regions related to the tumor area [41]. 

The existing data suggest that the most effective PNE program for BC patients should be administered by an experienced professional and last longer than current models. However, there is still a knowledge gap in optimizing this therapeutic approach. Undergoing cancer-related therapies is often overwhelming for BC patients. As a result, they often neglect the “side” aspects of their disease due to their busy schedules and main focus on the cancer diagnosis and cure, even in the early setting [8]. Addressing these issues by exploring additional management strategies is crucial. In this context, the implementation of a PNE program for early TNBC patients could be very interesting, as these women are often young and active patients who might be more receptive to educational interventions aimed at promoting their overall well-being and active role in society.

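### Selecting on a recent NRS of at least 4 and comparing each patient only with her own baseline cannot separate a PNE effect from regression to the mean, natural course or standard care

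*Protocol article*

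**What the plan says.** Section 2.2 describes the screening: "They will be given a web link to complete a monthly pain questionnaire". Patients with an NRS of at least 4 "will be invited to join the study within 4 weeks of the onset or worsening of the pain syndrome". Section 2.3 repeats the criterion for consecutive enrolment and lists NRS as the pain measure at T0, T1, T2 and six months after the programme.

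Section 2.1 describes a single cohort: "This mono-centric, observational, prospective, pilot cohort study is being led by IRCCS Humanitas Research Hospital". Section 2.4 asks whether the programme "can lead to clinical improvement in terms of QoL and pain in patients with early-stage TNBC". Section 2.7.2 sets the comparison: "The expected overall clinical improvement will be assessed based on the variation in the total scores of the administered assessment questionnaires at different timepoints". It then labels the result: "A positive response to PNE is defined as a 50% or greater improvement in patient-reported outcomes". The only between-group analysis is of biomarkers in responders and non-responders, all of whom received PNE. The Discussion describes the study as "providing data on the efficacy of PNE in reducing pain" and presents the NRS threshold as the answer to a selection problem in other trials. Regression to the mean is not mentioned.

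**The concern.** A patient chosen because a fluctuating score has just been high will, on average, score lower next time even if nothing is done. Here the selecting variable is also an outcome, entry is tied to recent onset or worsening, and no untreated course serves as a reference. Patients also receive standard care and may change their analgesia. A fall in NRS, or a share of patients improving by 50%, therefore mixes any PNE effect with selection, natural course and co-treatment.

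Three things are at stake:
- **Primary objective.** It is worded as a question about what the programme causes.
- **Go decision.** Under the Discussion, the randomised trial follows if the project's outcomes are reached.
- **Biomarker analysis.** Its responder group would include patients whose scores merely fluctuated.

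**Working it through.** The article gives no expected change, SD or reference response rate, so there is no figure of its own to reproduce. The check asks what the planned analysis would show if PNE did nothing and there were no time trend.

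**Inputs.** From the article: entry at NRS ≥4 on a 0–10 scale, response at ≥50% improvement, 30 evaluable patients. Assumed: NRS mean μ of 2–4 among surveyed patients, SD σ = 2.5, correlation r of 0.4–0.8 between any two ratings.

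**Analytic check, survey score used as T0.** A rounded score of at least 4 means an underlying value of at least 3.5. With z = (3.5 − μ)/σ and λ = φ(z)/(1 − Φ(z)), the expected fall is (1 − r)·σ·λ.
- μ = 2, r = 0.4: z = 0.6, λ = 0.333/0.274 = 1.215; fall = 0.6 × 2.5 × 1.215 = 1.82.
- μ = 3, r = 0.6: z = 0.2, λ = 0.391/0.421 = 0.929; fall = 0.4 × 2.5 × 0.929 = 0.93.
- μ = 4, r = 0.8: z = −0.2, λ = 0.391/0.579 = 0.675; fall = 0.2 × 2.5 × 0.675 = 0.34.

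**Simulation.** Ratings were rounded and limited to 0–10, and a responder has T2 no more than half of T0. A T0 of 0 counts as not improved.

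| How T0 NRS is obtained | μ=2, r=0.4: fall; responders | μ=3, r=0.6: fall; responders | μ=4, r=0.8: fall; responders |
|---|---|---|---|
| Qualifying survey score | 1.8; 44% | 0.9; 24% | 0.4; 9% |
| Re-measured, again ≥4 | 1.4; 34% | 0.7; 17% | 0.2; 5% |
| Re-measured, no second threshold | 0.0; 25% | 0.0; 15% | 0.0; 5% |

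The simulated falls in the first row agree with the formula. In the middle case of that row the mean goes from 5.35 to 4.41. With 30 patients, a two-sided 5% paired test would call such a null change significant in about 70% of studies. The article names no such test, so this only illustrates how little a non-zero change would prove.

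**Modelling new onset directly.** A separate run required the previous month to be below 4 and the current one at least 4, assuming SD 2.2, mean 3 or 4 and correlation 0.5–0.8. With the survey score as T0, the mean fall was 0.9–1.5 points with 21%–38% responders.

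**Allowing a trend.** In the middle case of the first row, an assumed upward drift of 1 point gives 5.35 to 5.38, that is no fall, and responders drop from 24% to 12%.

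**The case against.** A reader might infer that the design guarantees a fall, that patients enter at their pain peak, or that natural recovery will be reported as efficacy. The documents do not support this. The Introduction describes postoperative pain often lasting beyond three months, taxane neuropathy persisting in up to 40–50% of patients at six years, and oncologic treatment that may intensify pain. The drift calculation shows that such a course can cancel the selection effect. An NRS of at least 4 is a moderate level at a flare, not a demonstrated peak.

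Other parts of the opposing case also stand:
- The article does not say that the survey score is T0. The T0 visit, with its questionnaires and blood draw, may well include a fresh rating, which removes the mean shift if no second threshold applies.
- The 50% rule covers patient-reported outcomes generally. BR23, HADS, HIT-6 and MIDAS are not selection variables, so the percentages above describe NRS only.
- A single arm is legitimate for a pilot, the follow-on trial is to be randomised, and nothing says that its effect size will come from this study.

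This does not rescue the efficacy wording. Adjusting for analgesic changes deals with a co-treatment, not with selection or natural course. An uncertain natural course makes an uncontrolled change harder to interpret, not easier. Even with a fresh T0 and no second threshold, fluctuation alone produces some responders.

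**Conclusion.** The point holds as a limit on what the study can conclude. Selection on recent NRS together with a purely within-patient comparison means that a PNE effect cannot be separated from regression to the mean, natural course and standard care. Under no effect and no trend, how T0 is obtained decides whether the mean NRS fall is about 0 or as much as 1.8 points. The share meeting the 50% rule on NRS lies between 5% and 44% across all cases. These ranges rest wholly on the assumed mean, SD and correlation. Worsening under treatment would reduce them and recovery would add to them. The design itself is acceptable for a pilot; the efficacy and response-to-PNE reading attached to it is not.

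**What to change.** 1. State that NRS change is computed from a T0 rating taken separately from the qualifying survey score, with no second threshold on that rating. This costs one sentence and may already be the practice. Some patients will then start below 4 (mean T0 about 4.4 rather than 5.35 in the middle case), so say how a T0 of 0 counts under the 50% rule.
2. In the analysis section and the Discussion, replace efficacy and response to PNE with change, or 50% improvement, under PNE plus standard care. State that the responder rate has no control reference. Do not treat a non-zero mean change or the responder rate as evidence of a PNE effect, or as the effect size for the follow-on randomised trial. This costs only wording.
3. Optionally, with consent, report the monthly NRS course of eligible patients who do not join. This needs consent wording and a small descriptive table. Keep it descriptive and do not present an adjusted treatment difference, because the group is self-selected and may be small.

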### 2.6. Serum Marker Evaluation

At timepoints T0 and T2, peripheral venous blood samples will also be collected to carry out a panel of blood chemistry tests to research biomarkers that may correlate with PSs and/or with the response/non-response to PNE. Specifically, based on the data in the literature, serum levels of CRP, ESR, IL-6, IL-8, TNF-α, and CGRP will be measured. CRP and ESR will be determined according to the standard method currently used at the IRCCS Humanitas Research Hospital clinical analysis laboratory. IL-6, IL-8, TNF-α, and CGRP will be assessed through an enzyme-linked immunosorbent assay (ELISA) following the manufacturer’s instructions, as reported elsewhere [17,39].

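### NSAIDs or steroids started between T0 and T2 can bias the responder/non-responder marker contrast, in an unknown direction, and the biomarker model should carry a drug-class term

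*Protocol article*

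**What the plan says.** Section 2.2 sets the entry condition that "patients on any analgesic therapy will be recruited only if the therapy is stable for at least 3 months". After entry, "Patients will be allowed to modify their pain management strategies, including analgesic medications, as needed". Changes are documented and the patients stay in the analysis, "with appropriate statistical adjustments made to account for any changes in their analgesic use, assessed by applying an equianalgesic scale". The same section counts as pain therapies drugs "including non-steroidal anti-inflammatory drugs, steroids, opioids".

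Section 2.6 states that "serum levels of CRP, ESR, IL-6, IL-8, TNF-α, and CGRP will be measured", with blood drawn at T0 and T2; section 2.3 adds the neutrophil-to-lymphocyte ratio. One secondary objective in section 2.4 is whether "serum levels of inflammatory biomarkers before and after PNE treatment correlate with the response to PNE".

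For that objective section 2.7.2 compares the T0 to T2 marker change between responders (at least 50% improvement in patient-reported outcomes) and non-responders. It uses a generalized linear model in which "the factors involved in the analysis will be the groups (responders/non-responders) and the timepoints (intra-group variable". The covariates listed are demographics, education, comorbid conditions, breast cancer risk factors and menopausal status. Then: "Additional covariates to be considered include anxiety and depression". Analgesic use appears in neither place.

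**The concern.** The entry rule and the freedom to change analgesia later are both reasonable. Together they mean that new drug treatment of the index pain will mostly begin after T0, between the two blood draws. Two of the three drug classes that section 2.2 names, NSAIDs and steroids, can act on the inflammatory markers as well as on pain. The response definition sets no condition on new medication, so starting such a drug can influence both which group a patient falls into and what her markers do.

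The study has no control group, so the responder/non-responder contrast is the only comparison for this objective. The one metric named for handling analgesic changes is built around pain relief. Two patients with the same score could have started an opioid and an NSAID, with different marker consequences. If the contrast is read without regard to drug class, a drug effect could appear as a link between markers and response to PNE, or could hide a real one.

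**Working it through.** The article gives no figure for drug uptake, drug effect, marker variability or significance level, so there is no plan figure to reproduce. What follows shows what could happen under stated assumptions.

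**Step 1. The mechanism.** Let b be the marker fall caused by the drug, in SDs of marker change. Let p_R and p_N be the shares of responders and non-responders who started it. With no PNE effect on markers, the expected group difference is

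difference = -b x (p_R - p_N).

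With start share q and response probabilities r1 (with the drug) and r0 (without):

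p_R = q r1 / [q r1 + (1 - q) r0]; p_N = q(1 - r1) / [q(1 - r1) + (1 - q)(1 - r0)].

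Example (all assumed): q = 0.20, r1 = 0.70, r0 = 0.25, b = 1.
- p_R = 0.14/0.34 = 0.41
- p_N = 0.06/0.66 = 0.09
- difference = -0.32 SD

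Simulation with 30 patients gives -0.33 SD and 12% false positives at 5%, against 4% with a drug term. With q from 0.10 to 0.40, r1 from 0.50 to 0.70 and b from 0.5 to 1.0, the difference runs from about -0.05 to -0.44 SD. False positives run from about 5% to 18%, and from 4% to 6% with a drug term.

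**Step 2. Response as a 50% fall in NRS, starts unrelated to pain course.** From the documents: 30 evaluable patients, possibly 50 (section 2.7.1), and entry at NRS 4 or more (section 2.2). Assumed:
- baseline NRS 4 to 8, with probabilities 0.30, 0.25, 0.20, 0.15, 0.10;
- mean fall of 1 point without the drug, SD of change 2;
- drug effect d NRS points; no PNE effect on markers.

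| Start share | n | d | b | False difference | Rejection at 5% |
|---|---|---|---|---|---|
| 50% anti-inflammatory | 30 | 2 | 1 | -0.37 SD | 14% |
| same | 30 | 2 | 1.5 | -0.54 SD | 22% |
| same | 50 | 2 | 1 | -0.36 SD | 20% |
| 25% anti-inflammatory, 25% opioid | 30 | 2 | 1 | -0.18 SD | 7% |
| same | 30 | 1 | 1 | -0.09 SD | 5.4% |

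In the first row 71% of responders and 35% of non-responders are starters, so -1 x (0.71 - 0.35) = -0.36, in line with the simulation. Rates are per marker.

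**Step 3. Starts driven by pain.** Changes are made as needed, so patients with a worse course are more likely to start. The first row of the table was rerun with the log-odds of starting raised per SD of worse drug-free course:

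| Log-odds per SD | False difference | Rejection at 5% |
|---|---|---|
| 0.5 | -0.19 SD | 7.2% |
| 1.0 | -0.08 SD | 5.2% |
| 1.5 | +0.02 SD | 5.8% |
| 2.0 | +0.08 SD | 5.3% |

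With a 1-point drug effect the sign is already positive at log-odds 1.0 (+0.13 SD, 5.3%). In a stronger setting (1-point relief, 1.5 SD marker effect, strongly pain-driven starts) the result was +0.48 SD with 16% rejection.

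**Step 4. What the adjustment score does.** In the 25% plus 25% setting with d = 2 and b = 1, starts unrelated to pain:
- no score: -0.18 SD, 7%;
- a score that counts opioids only: -0.26 SD, 10%;
- a relief score that truly covers every analgesic: 0.00 SD, about 5%;
- a term for anti-inflammatory start: 0.00 SD, 5%.

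**Step 5. The drug-class term.** In every setting of steps 2 and 3 it brought the difference to about 0 SD and rejection to about 5%.

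**The case against.** Four points against the concern carry weight.

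- **Direction.** A reader might infer that the plan will produce a false link in which responders show larger marker falls. That needs starts unrelated to the pain course. Section 2.2 says changes are made as needed, and section 2.3 gives standard of care according to pain level; step 3 shows this can cancel or reverse the bias. The objection stands: the direction is not established.
- **The scale.** A reader might infer that starting an NSAID or steroid would be scored as no change. The text does not say so. It names no particular scale, does not limit it to opioids, and applies it to any analgesic change. A score that really covered all analgesics would remove the bias in step 4, because there drugs influence response only through relief. What remains is that the scale records relief and not class, and the plan gives no way of placing NSAIDs and steroids on it.
- **The covariate list.** A reader might infer that the model rules out any analgesic adjustment. The list is worded openly, section 2.2 promises adjustment, and an analysis plan could supply the term. Even so, a plan that followed section 2.2 as written would carry the relief metric into the marker analysis.
- **Response definition.** It refers to patient-reported outcomes, not NRS alone. A broader definition would weaken the link between a new drug and response.

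A reader might also infer that a drug-driven marker would be taken into the later trial. The Discussion proposes validating the programme and mentions no marker being carried forward. CGRP-acting drugs appear only as background in the Introduction; the point rests on NSAIDs and steroids.

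**Conclusion.** The concern holds in limited form. The documents establish that analgesic changes are allowed between the blood draws, that the named metric concerns pain relief, that NSAIDs and steroids are among the drugs in play, and that the stated biomarker model names no analgesic term. Bias in the responder/non-responder marker contrast is therefore possible.

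Its size and sign are unknown. Under the assumed inputs it is about -0.4 SD (rejection 14%) when half the cohort starts an anti-inflammatory irrespective of pain course, and near zero or positive when patients doing badly start. With rare use or weak drug effects it is negligible. A claim of a known false-positive rate, or of a bias always favouring a PNE-marker link, would go beyond the documents.

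The case for acting does not depend on the sign, because the same term handles both directions in the settings tried. It concerns one secondary, exploratory objective of a pilot and is worth changing for that reason alone.

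**What to change.** **Section 2.2.** Keep the equianalgesic scale for pain relief. When documenting each change, also keep the drug class: NSAID, steroid, and any CGRP-acting drug, coded separately where numbers allow, and whether it was started or increased, unchanged, or stopped or reduced between T0 and T2.

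**Section 2.7.2.** Add change in anti-inflammatory use and its interaction with timepoint to the biomarker model. Repeat the model without patients who changed such a drug as a sensitivity analysis.

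Eligibility and permitted analgesia stay as they are.

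**Cost.** No new visit or measurement, since changes are already documented, and one extra model term. In the 50% scenario, with a simulated responder share of 0.425, the correlation between response and drug start is 0.36 x sqrt(0.425 x 0.575)/0.5 = 0.356. The standard error of the responder contrast grows by 1/sqrt(1 - 0.127) = 1.07, about 7%. With 30 patients, separate class terms may not be estimable and would have to be pooled, which assumes that the classes share one effect per marker. The sensitivity set will be small.
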